**Figure 6 figure6:**
[figure not shown]
Screen captures of WittyFit mobile app (French version). Left screen: homepage; middle screen: body shape to self-report musculoskeletal disorders; right screen: gaming and trophies are incentive strategies for workers to complete questionnaires.

### Statistical Considerations

#### Sample Size Calculations

Using only Internet or computer interventions for behavior change outcomes improving eating disorders and nutrition [76], weight and cardiorespiratory fitness [77], or mood [78] and stress related to the workplace and performance and productivity [79], the sample size estimation was performed according to Cohen’s recommendations with the following defined effect size (ES) bounds: small (ES 0.2), medium (ES 0.5), and large (ES 0.8, “grossly perceptible and therefore large”) [80]. Considering an effect size of 0.33, a 2-tailed type I error fixed at a=0.001 to take into account multiple comparisons, and a moderate loss to follow-up rate, N=1000 participants will allow us to highlight (1) such ES for a statistical power greater than 95% for paired comparisons (n=225 with a correlation coefficient of .5) and (2) such ES for a statistical power greater than 80% for intergroup comparisons (n=311 by group).

For life expectancy, 100,000 workers followed over 5 years would provide a sufficient and relevant sample size to achieve the long-term objectives measured by this study. Purposive sampling will be conducted to best draw comparisons with previous research [81] studying leisure time spent sitting in relation to total mortality in a prospective cohort of US adults [9] and to further elucidate job strain among blue-collar and white-collar employees. Job strain has previously been associated with total mortality in a 28-year cohort study [82]. To address the objective of reducing premature mortality, statistical power estimation was based on a hazard ratio used for censored data (hazard ratio of 1.25 and 2) and in accordance with previously described data. This hazard ratio estimate was proposed to support a type I error of 5% (2-sided) with statistical power at 95% (see Figure 7). However, the study will be unlimited within the long-term aspects of its epidemiological design.

**Figure 7 figure7:**
[figure not shown]
Sample size estimation for life expectancy based on simulations about hazard ratios for censored data as mortality (2-sided type I error of 5% and statistical power 95%).

#### Overall Statistical Analyses

Statistical analysis will be performed using Stata version 13 software (StataCorp LLC). All statistical tests will be 2-sided, and *P*<.05 will be considered significant. Quantitative variables will be described in terms of numbers, average, median, standard deviation, and range.

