#### Analyses of Shorter Term Objectives

To study WittyFit’s effect on morbidity and well-being, analyses will include comparisons with historical cohorts and literature and within the paired data from individual participants as they generate their own basis for comparison. To study longitudinal evolution of parameters associated to morbidity and well-being, models for repeated measures will be performed using a random-effects model (linear or generalized linear) along with fixed effects for descriptive data (eg, gender, age, body mass index, type of contract [full-time, part-time], professional roles [unskilled, skilled, mid-level workers, and senior executives] and occupational sector [commercial activities and service, health and social services, manufacturing/blue collar industries, finance officers]) taking into account within and between participant variability and company variability. All effect sizes will be presented with 95% confidence intervals.

When appropriate, comparisons between subgroups described above will be performed. Typical statistical tests will be applied: chi-square or Fisher exact tests for comparisons between groups from categorical parameters and analysis of variance or Kruskal-Wallis test for quantitative variables. The Shapiro-Wilk test will be used to assess normality, and the Fisher-Snedecor test to assess homoscedasticity. For censored data, the time-to-event curves will be estimated with the use of the Kaplan-Meier method. Comparisons will be performed by log-rank test. Then, Cox proportional-hazards regression models will be considered to study the prognostic factors in a multivariate situation by backward and forward stepwise modeling on the factors considered significant in univariate analysis and in accordance with parameters of clinical relevance [83,84]. The proportional-hazard hypothesis will be verified using Schoenfeld’s test and plotting residuals. The interactions between possible predictive factors will also be tested. Results will be expressed as hazard ratios and 95% confidence intervals. Considering repeated correlated censored data, marginal models may be preferred.

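### The shorter-term comparisons are sized at a two-sided alpha of 0.001 for multiplicity, but the stated decision rule calls every test significant at P<.05

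*Protocol article*

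**What the plan says.** Under Sample Size Calculations, the shorter-term comparisons are planned with "a 2-tailed type I error fixed at a=0.001 to take into account multiple comparisons" and a standardised effect of 0.33. Two results follow: more than 95% power for paired comparisons with 225 workers (correlation .5), and more than 80% power for intergroup comparisons with 311 per group. The same section sizes the mortality objective separately, at a two-sided 5% with 95% power.

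Under Overall Statistical Analyses, one rule covers everything: "All statistical tests will be 2-sided, and *P*<.05 will be considered significant". Under Analyses of Shorter Term Objectives, the reporting rule is "All effect sizes will be presented with 95% confidence intervals". That section also plans subgroup comparisons, interaction tests and stepwise selection on factors found significant in univariate analysis. Neither these sections nor the ones on longer-term objectives and missing data mention 0.001 or any named adjustment.

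**The concern.** The article decides that multiple comparisons need control and builds that control into the planning alpha. It then gives a decision rule for all tests that contains no such control. Both statements cannot govern the shorter-term comparisons: a well-being change with P=.03 counts as significant under one and not under the other.

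The choice has consequences here. The Objectives section says the study will demonstrate improvement in well-being and morbidity across three behavioural categories, which the Behavioral Outcomes section divides into 11 subcategories, with addiction to be added. Visual analog scales are prompted every 15 days and detailed questionnaires every 6 months. The article ranks no shorter-term outcome above the others, so the threshold largely determines which results are presented as demonstrated.

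**Working it through.** **Inputs.** From Sample Size Calculations: two-sided alpha 0.001, ES 0.33, paired n=225 with r=.5 and power above 95%, intergroup n=311 per group and power above 80%. From Overall Statistical Analyses: two-sided .05 for all tests. From Behavioral Outcomes: 4 physical + 2 mental + 5 work-related = 11 subcategories.

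**Step 1: reproduce the plan's sample sizes (normal approximation).** With r=.5 the SD of the difference is sqrt(2(1−.5)) = 1 SD.

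- Paired: n = 2(1−r) × ((z_alpha/2 + z_power)/ES)².
  - alpha 0.001: ((3.291 + 1.645)/0.33)², giving 224 (stated 225).
  - alpha 0.05: ((1.960 + 1.645)/0.33)², giving 120.
- Two groups: n per group = 2 × ((z_alpha/2 + z_power)/ES)².
  - alpha 0.001: 2 × ((3.291 + 0.842)/0.33)², giving 314 (stated 311).
  - alpha 0.05: 2 × ((1.960 + 0.842)/0.33)², giving 145.

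The t-based versions at 0.001 are 230 and 317. All the 0.001 results lie within 3% of the stated figures; the .05 results do not come close. The planning alpha really was 0.001.

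**Step 2: power at the stated n under each threshold (normal approximation).**

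| Comparison | alpha .001 | alpha .05 |
|---|---|---|
| 225 pairs | 95.1% | 99.9% |
| 311 per group | 79.5% | 98.4% |

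Testing at .001 therefore gives the stated power to rounding. The 79.5% against a claim of more than 80% is too small a gap to raise.

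**Step 3: distance between the two rules.** 0.05/0.001 = 50.

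**Step 4: illustrative family-wise error.** Assume one independent test per listed subcategory at one time point. The chance of at least one false positive is 1 − (1 − alpha)^11.

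- alpha .05: 1 − 0.95^11 = 0.431.
- alpha .001: 1 − 0.999^11 = 0.011.

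**Step 5: smallest observed change that reaches significance with 225 pairs.** Critical value divided by sqrt(225) = 15.

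- alpha .05: 1.960/15 = 0.131 SD.
- alpha .001: 3.291/15 = 0.219 SD.

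Observed changes between about 0.13 and 0.22 SD would be declared significant under the stated rule and not under the design alpha. All of them are below the planned 0.33.

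**The case against.** The best defence is that a planning alpha and a general reporting convention serve different purposes. On this view the .05 sentence is boilerplate, and the adjustment may stand in the full protocol (Multimedia Appendix 1) or an analysis plan, neither of which is shown. This part stands: a reader might infer that the planned error control will never reach the results, and a condensed article cannot show that. It does not remove the conflict, because the sentence covers all tests without exception and the 95% intervals agree with .05, not with .001. The point concerns a rule that is stated, not detail that is left out.

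Second, the study is called exploratory in the Abstract and under Ethics, which could justify unadjusted tests. That is a legitimate choice, but the article itself gives multiplicity as the reason for 0.001, so one of the two sections must change either way.

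Third, the size of the problem can be overstated in several ways.

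- A reader might infer that false positive improvements are close to certain at .05. For 11 independent tests the figure is 43%, and it counts errors in both directions; for false improvements alone it is 1 − 0.975^11 = 24%. A figure of 92% needs 50 independent tests, a count the article never gives and which is only 0.05/0.001 worked backwards. The Introduction and Discussion describe the outcomes as linked, and positive correlation would generally lower these rates.
- Adding the two intergroup samples to get 622 pairs would give smaller critical changes, but the article's paired n is 225.
- A reader might infer that a stricter alpha makes observed improvements trustworthy. It does not address time trends or regression to the mean in within-person and historical comparisons.
- It is tempting to say that participants were spent on protection that is then thrown away. The Participants section sets no sample size limit, so N=1000 describes what can be detected and is not a recruitment price.

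**Conclusion.** The point holds as an internal contradiction. The shorter-term paired and intergroup comparisons have a design alpha of 0.001, justified by multiplicity, and a stated decision threshold 50 times larger, with no other adjustment in the article. That both statements were made, and that the stated sample sizes come from 0.001, needs no assumption beyond the article's own inputs.

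The consequences are illustrative. The 43% against 1.1% assumes 11 independent tests, one per listed subcategory at a single time point. The article does not say how many comparisons 0.001 was meant to cover; repeated measurement and subgroups would add tests, while correlation would generally reduce the rates. The 0.13 against 0.22 SD holds for 225 pairs with r=.5.

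The scope is limited to the shorter-term objectives. The mortality calculation uses a two-sided 5% and agrees with the general rule. A true effect near 0.33 would usually be detected under either threshold, so what is affected is the status of smaller observed changes. The documents do not show that the final analysis will lack multiplicity control, only that the rule as published does not contain it.

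**What to change.** In Overall Statistical Analyses, replace the blanket threshold:

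- Limit P<.05 to the mortality analysis, which was sized at that level.
- Use P<.001 for the shorter-term well-being, behaviour and morbidity comparisons. Alternatively, use Holm at a family-wise .05 over a fixed list with one named test and time point per subcategory. Holm is a different rule: with 11 tests its first step is .05/11 = .0045.
- In Analyses of Shorter Term Objectives, match the confidence level to the threshold: 99.9% intervals with .001, or intervals adjusted for the listed family with Holm.
- Name any intergroup comparison that is meant to be inferential. Label the economic, remaining subgroup and all other P values descriptive.

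If the sponsor prefers unadjusted exploratory testing, state that in Overall Statistical Analyses and remove the multiplicity rationale from Sample Size Calculations.

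The cost is a few sentences and, under the first route, fewer nominally significant results. No extra participants are needed, because the stated sizes already assume 0.001. The choice should be made before shorter-term results are analysed.

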#### Analyses of Shorter Term Objectives

To study WittyFit’s effect on morbidity and well-being, analyses will include comparisons with historical cohorts and literature and within the paired data from individual participants as they generate their own basis for comparison. To study longitudinal evolution of parameters associated to morbidity and well-being, models for repeated measures will be performed using a random-effects model (linear or generalized linear) along with fixed effects for descriptive data (eg, gender, age, body mass index, type of contract [full-time, part-time], professional roles [unskilled, skilled, mid-level workers, and senior executives] and occupational sector [commercial activities and service, health and social services, manufacturing/blue collar industries, finance officers]) taking into account within and between participant variability and company variability. All effect sizes will be presented with 95% confidence intervals.

When appropriate, comparisons between subgroups described above will be performed. Typical statistical tests will be applied: chi-square or Fisher exact tests for comparisons between groups from categorical parameters and analysis of variance or Kruskal-Wallis test for quantitative variables. The Shapiro-Wilk test will be used to assess normality, and the Fisher-Snedecor test to assess homoscedasticity. For censored data, the time-to-event curves will be estimated with the use of the Kaplan-Meier method. Comparisons will be performed by log-rank test. Then, Cox proportional-hazards regression models will be considered to study the prognostic factors in a multivariate situation by backward and forward stepwise modeling on the factors considered significant in univariate analysis and in accordance with parameters of clinical relevance [83,84]. The proportional-hazard hypothesis will be verified using Schoenfeld’s test and plotting residuals. The interactions between possible predictive factors will also be tested. Results will be expressed as hazard ratios and 95% confidence intervals. Considering repeated correlated censored data, marginal models may be preferred.

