## Methods

### Ethics

This exploratory interventional cohort study in an ecological situation received approval from the ethics committee of the University Hospital of Clermont-Ferrand, France, and has been registered at ClinicalTrials.gov [NCT02596737]. See Multimedia Appendix 1 for the original protocol.

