### Outcomes

#### Behavioral Outcomes: Three Major Health-Related Categories (WittyFit)

Workers will answer validated questionnaires within three major health-related behavioral categories: physical, mental, and work-related well-being (Textbox 1). Each main category is divided in subcategories:

Physical well-being investigates nutrition, physical activity, sleep, and musculoskeletal function. Nutrition will be assessed through 24-hour recalls of food intake. Physical activity combines questions about time spent in activity at work and leisure, as well as estimates of sedentary behavior time. This category also includes a questionnaire on sleep quality and quantity [46]. Musculoskeletal function is based on an adapted version of the Nordic Musculoskeletal Questionnaire [64].Mental well-being explores stress and mood. We will use the validated Hospital and Anxiety Depression Scale [65] and the visual analog scale of stress [66,67]. Questions on smoking and addiction will be added later.Work-related health questions explore job strain, latitude/decision-making, work organization and tasks, social support, and recognition. We will use the validated Job Demand-Control-Support model of Karasek [18-20] and the effort reward model of Sieigrist [21-23] with the addition of some specific questions such as visual analog scales (demand, control, etc) that we want to further validate.

Participants complete questionnaires at times convenient to them; however, participants will be prompted to complete a general visual analog scale from the main categories and major subcategories every 15 days and the more detailed questionnaires every 6 months. When a significant difference appears on the latest visual analog scale, the user is asked to complete specific questionnaires linked with the problem detected by the visual analog scale. Gaming and trophies are incentive strategies for workers to fulfill questionnaires.

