#### Analyses of Longer Term Objectives

Decreased premature mortality is the long-term goal of the development of the WittyFit software. Considering this censored data, estimation will be performed as described previously using the Kaplan-Meier approach. Comparison with historical cohorts and previous research will be included in the estimates of 95% confidence intervals. WittyFit’s effect will be also studied using log-ranked comparisons and a Cox proportional hazards model. Multivariate models will be used according to univariate results and clinical and epidemiological relevance.

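### Adjustment in the mortality model depends partly on univariate results and smoking is not yet collected, so WittyFit's estimated mortality effect is at risk of residual confounding

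*Protocol article*

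**What the plan says.** The Ethics section calls the design an "exploratory interventional cohort study in an ecological situation". Under Participants, any worker who agrees may join. There is no randomisation, and the Objectives section makes lower premature mortality the primary long-term aim.

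Three statements bear on confounder control:

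- **Analyses of Longer Term Objectives.** WittyFit's effect is to be studied with "log-ranked comparisons and a Cox proportional hazards model". On adjustment: "Multivariate models will be used according to univariate results and clinical and epidemiological relevance". There is also an external comparison: "Comparison with historical cohorts and previous research will be included in the estimates of 95% confidence intervals".
- **Analyses of Shorter Term Objectives.** For censored data, Cox models serve the search for prognostic factors, using "backward and forward stepwise modeling on the factors considered significant in univariate analysis". The same sentence names a second criterion for what enters the model, namely that the choice be made "in accordance with parameters of clinical relevance". The covariates that this section names (gender, age, body mass index, contract, role, sector) belong to the repeated-measures models and do not include smoking.
- **Behavioral Outcomes.** "Questions on smoking and addiction will be added later". No date is given. Textbox 1 likewise marks addiction as still to come. Yet the Manager Feedback section gives help with quitting smoking as an example of what managers may do with the tool.

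**The concern.** A univariate P value is a poor criterion for choosing confounders. A variable can confound the exposure effect without being significant alone, and an interval computed as if the chosen model had been fixed in advance ignores the choice. In a randomised trial this would mostly affect precision. Here the effect estimate itself depends on it.

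Smoking is the clearest case: it bears on premature death, may differ between people who take up a health programme and those who do not, and is something the programme may change. A current-smoking answer given by an early participant after months of use is a post-exposure measurement and cannot stand in for baseline status. At stake are whether an apparent mortality benefit can be credited to WittyFit, and whether a change in smoking can be assessed at all in early entrants.

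**Working it through.** **1. The plan's own mortality figures.** The sample size section gives hazard ratios of 1.25 and 2, a two-sided 5% error, 95% power, and 100,000 workers over 5 years. Events needed with equal groups (Schoenfeld) are D = 4(1.960 + 1.645)² / (ln HR)². This gives 1,044 for HR 1.25 and 109 for HR 2. The 100,000 can be neither reproduced nor refuted, because baseline mortality and group split are not in the text and Figure 7 is not shown. If annual mortality is 0.05% to 0.3% (assumed), 100,000 × 5 years yields 250 to 1,500 deaths. Both a small and a large event count therefore have to be considered.

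**2. Bias from leaving out smoking.** With no true effect, and smoking unrelated to the other covariates, the apparent hazard ratio is approximately

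[1 + p₁(RR − 1)] / [1 + p₀(RR − 1)],

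where p₁ and p₀ are smoking prevalence in users and comparator and RR is the mortality ratio for smoking. The documents give none of these, so all are assumptions.

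| RR | p₁ vs p₀ | Calculation | Apparent HR |
|---|---|---|---|
| 2 | 25% vs 30% | 1.25 / 1.30 | 0.96 |
| 2 | 20% vs 30% | 1.20 / 1.30 | 0.92 |
| 3 | 25% vs 30% | 1.50 / 1.60 | 0.94 |
| 3 | 20% vs 30% | 1.40 / 1.60 | 0.875 |

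A wider grid runs from 0.98 (RR 1.5, 20% vs 25%) to 0.77 (RR 3, 15% vs 35%).

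**3. Against the planned effect and precision.** On the log scale the table spans −0.039 to −0.134. The smaller planning effect is ln 1.25 = 0.223, so the bias is 18% to 60% of it. At 1,044 deaths in equal groups the standard error of the log hazard ratio is 2/√1,044 = 0.062, so the bias is 0.6 to 2.2 standard errors. A nominal 5% test would then reject a true null about 10% to 58% of the time. At 250 deaths the standard error is 0.126 and the rejection rate is 6% to 18%. A larger study makes this worse, so the reliance on sample size under Quality Control Measures gives no protection.

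**4. What the selection rule adds.** A simulation used a true odds ratio of 1.00, a logistic approximation to a rare-event Cox model, six modest confounders all acting in one direction, and smoking with an odds ratio of 2 for death. It compared a fixed adjustment set with univariate screening plus backward selection at P<.05. All strengths are assumed.

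| Model | About 160 deaths: OR, coverage | About 1,080 deaths: OR, coverage |
|---|---|---|
| Fixed set, with smoking | 0.995, 95.0% | 0.998, 93.3% |
| Selection, with smoking | 0.91, 91.2% | 0.994, 93.3% |
| Fixed set, no smoking | 0.93, 94.3% | 0.94, 85.3% |
| Selection, no smoking | 0.85, 83.3% | 0.93, 83.3% |

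The simulation error of the coverages is about 1 to 2 percentage points on the left (400 runs) and 2 to 3 on the right (150 runs). With few deaths, selection shifts the estimate and lowers coverage. Most of that loss is bias: the mean standard error after selection was 0.165 against a true spread of 0.171, so the interval is only slightly too narrow. With about 1,080 deaths, selection makes no visible difference and omitting smoking does the damage.

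**The case against.** A reader might infer that the mortality effect will be estimated by stepwise selection and will therefore be confounded, with intervals that are too narrow. The documents do not support that.

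- The stepwise sentence stands in the shorter-term section, is written for prognostic factors, and is qualified by clinical relevance. The mortality section does not mention stepwise selection; its reference back to earlier methods attaches to the Kaplan-Meier estimate.
- Both sections admit clinical relevance as a criterion, so age, sex or smoking may be kept whatever their P value.
- Smoking is deferred, not excluded. If the item arrives before extension beyond the first 200 workers, those affected are 200 of 100,000, or 0.2%.
- The size and direction of any bias rest on assumed inputs. Nor can one say that confounding would exceed any plausible benefit, since the documents give no benefit to compare it with.
- A detailed covariate list may sit in the full protocol in Multimedia Appendix 1, which is not at hand.

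The first four stand and limit the point to a risk. The last stands only in part: the point is not that a list is absent, but that the article states a rule giving univariate results a role in choosing confounders. The relevance clause permits good adjustment but guarantees no covariate. With the smoking item undated and enrolment begun in January 2016, the number without baseline smoking is unknown.

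**Conclusion.** The point holds as a risk of residual confounding in the primary long-term analysis and should be addressed. The rule for the mortality model lets univariate results influence adjustment in a non-randomised comparison, and smoking is not collected at entry.

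For smoking alone, a null effect would appear as a hazard ratio of about 0.96 to 0.88, given a smoking mortality ratio of 2 to 3 and prevalence of 20-25% in users against 30% in the comparator. The direction rests on the assumption that users smoke less. Selection matters mainly if deaths are few, where it may bias the estimate and leave intervals somewhat too narrow. Near the 1,044 deaths that the plan's HR of 1.25 requires, it adds little and missing smoking is the main problem. Participants who enrol after the item is added can be adjusted.

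**What to change.** 1. In Analyses of Longer Term Objectives, fit the WittyFit effect with one pre-specified adjustment set chosen on subject matter and kept regardless of P value: age, sex, role, sector, contract, body mass index and smoking.
2. In Analyses of Shorter Term Objectives, confine univariate screening and stepwise modelling to exploratory prognostic models, and say that they do not determine the adjustment for WittyFit's effect.
3. Add one smoking-status item (never, former, current) to the entry questionnaire before extension beyond the first company.
4. Include baseline chronic disease only if the WittyFit Research database can be used for this analysis. The Medical Outcomes section keeps it apart from the behavioural database, so it may need a linkage step.

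The cost is one extra question and some changes of wording. For those already enrolled, smoking would be recorded late or missing, and baseline status recoverable only by recall. The comparisons with historical cohorts and literature benefit only where the comparator also reports smoking.
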